### Health economics

A service use questionnaire (Table 3) piloted in the feasibility trial will be used to collect resource use at baseline and at the 1‐ and 6‐month follow‐ups, and will include both the cost of providing the interventions and the costs of patient healthcare utilization. Quality‐adjusted life years (QALYs) [52, 53] will be calculated using responses from the EuroQol five‐dimensional five‐level questionnaire (EQ‐5D‐5L) administered at baseline and at the 6‐month follow‐up.

**TABLE 3 add70115-tbl-0003:** Service use questionnaire.

In the past month, how many times have you used the following health services that were NOT provided by the ESCAPE trial?		
	For smoking cessation/reduction	For any other purposes
	(Please enter the number of times you have used each service; if none, enter zero)	
Not in the hospital		
a. How many times have you seen your GP?	______times	______times
b. How many times have you seen a practice nurse?	______times	______times
c. How many times have you seen a pharmacist?	______times	______times
d. How many times have you attended a session with someone from a smoking cessation service?	______times	
e. How many times have you called the NHS Smoking Helpline service?	______times	
f. How many times have you seen a mental health worker in the community or at your home?	______times	______times
g. How many prescription items of the NRT product have you received?^a^	______ items	______ items
h. How many prescription items of Zyban (bupropion) have you received?	______ items	______ items
i. How many prescription items of Champix (varenicline) have you received?	______ items	______ items
j. How many prescription items have you received other than NRT, Zyban or Champix?	______ items	______ items
In the hospital		
k. How many times have you visited a hospital A&E department?		______times
l. How many times have you visited a hospital as an outpatient?		______times
m. How many times have you visited a hospital for a day case?^b^		______nights
n. How many nights have you stayed in a hospital as an inpatient?		______times
o. How many times have you been taken to the hospital by an emergency ambulance?		______times
p. None of the above	Yes	

^a^
One prescription item refers to a single prescribed medication, product or device on a prescription. If you have picked up the same medicine on several occasions over the period stated above, it counts as separate items for each occasion.

^b^
Day case: attended hospital for a procedure but stayed for less than 24 hours.

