### Economic evaluation

To determine the short‐term cost‐effectiveness of the intervention, we will undertake a within‐trial incremental cost‐effectiveness analysis to assess the value for money afforded by the intervention over and above usual care at 6 months, using data collected during the trial.

The resources used to provide the e‐cigarette starter kit intervention will be recorded alongside the trial. This includes staff time and materials used to train clinicians delivering the intervention, the provision of the e‐cigarette starter kit and the staff time spent on consultations. All participants will have access to usual care, and the use of currently available smoking cessation aids will be collected using a service use questionnaire piloted in the feasibility study at baseline, and at the 1‐ and 6‐month follow‐ups. Additionally, the participants' wider healthcare resource use in primary and secondary care will also be collected using the service use questionnaire. To generate cost profiles for each participant, unit costs derived from both the trial records and the most recent national average cost data will be applied to the quantities of corresponding resources used [57, 58]. QALYs will be calculated based on responses obtained from the EQ‐5D‐5L questionnaire using the ‘area under the curve’ approach, serving as the primary health outcome for the cost‐effectiveness analysis [52, 59]. We will assess patterns of missing data and assess the impact of missingness using multiple imputation methods [60].

A decision‐analytic model developed at the University of York will be adapted to project the long‐term cost‐effectiveness beyond the trial period [61]. Lifetime smoking‐attributable healthcare cost and expected QALYs associated with the two trial arms will be estimated using Markov models. The model will account for annual background abstinence for people who smoke and relapse for quitters, and an annual discount rate of 3.5% will be applied to both costs and QALYs [53, 62, 63]. For detailed methods, please refer to a previously published article [61].

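### The one-month recall in the service use questionnaire leaves healthcare use unobserved in months 2 to 5 of a 6-month cost-effectiveness analysis, and two hospital items print each other's answer unit

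*Protocol article*

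**What the plan says.** All references are to the Protocol article.

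- **Recall window.** Table 3 (Health economics) puts one question over every item: "In the past month, how many times have you used the following health services that were NOT provided by the ESCAPE trial". Its footnote on prescriptions points back to that same window: "If you have picked up the same medicine on several occasions over the period stated above". No second version with a longer window is shown for the 6-month visit.
- **Timing.** The questionnaire "will be used to collect resource use at baseline and at the 1‐ and 6‐month follow‐ups", and the schedule in Table 1 agrees.
- **Use.** The Economic evaluation section says that participants' "wider healthcare resource use in primary and secondary care will also be collected using the service use questionnaire". The within-trial analysis is meant "to assess the value for money afforded by the intervention over and above usual care at 6 months, using data collected during the trial". Unit costs "will be applied to the quantities of corresponding resources used".
- **Delivery costs.** The same section has staff training, the starter kit and consultation time recorded alongside the trial, so these do not depend on the questionnaire.
- **QALYs.** EQ-5D-5L is measured at baseline and 6 months and integrated by area under the curve.
- **Answer units.** Inpatient item n asks "How many nights have you stayed in a hospital as an inpatient" but its answer space is labelled *times*. Day-case item m asks for a number of times but is labelled *nights*. The table note defines a day case as lasting under 24 hours.

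**The concern.** A one-month look-back at 1 month and at 6 months sees only the first and last months of follow-up. Stop-smoking service contacts, prescriptions, outpatient visits and admissions in between are never asked about in either arm. The article gives an integration rule for QALYs but none for healthcare costs.

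The incremental cost has two parts that are captured differently. Delivery cost falls on the intervention arm and is fully recorded. Any difference in healthcare use, whether a saving or an excess, is seen for a third of the time. If the parts are combined without correction, the balance between them shifts, and so does the ratio that is compared with the £20,000–30,000 per QALY range. The exchanged units concern hospital items, where a stay entered as one admission instead of its nights would be under-costed.

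**Working it through.** There is no published figure to reproduce, so the check is a count of months followed by simple algebra.

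**1. Coverage.** A form at month *t* with one-month recall observes the interval (*t* − 1, *t*].

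| Form | Interval observed | Within 0–6 months after randomization |
|---|---|---|
| Baseline | (−1, 0] | 0 months |
| 1 month | (0, 1] | 1 month |
| 6 months | (5, 6] | 1 month |

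Observed: 1 + 1 = 2 of 6 months (33%). Not observed: (1, 5], 4 of 6 months (67%). If the 6-month form asked about the period since the 1-month form, coverage would be (0, 1] plus (1, 6], or 6 of 6.

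**2. If the two reports were added without scaling.** Let *d* be a constant monthly between-arm difference in healthcare cost and *K* the delivery cost.

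- Full incremental cost: *K* + 6*d*. As summed: *K* + 2*d*. Shortfall: 4*d*.
- The healthcare part counts at 2*d*/6*d* = one third; *K* counts in full.
- For *d* > 0 the relative understatement is 4*d*/(6*d* + *K*). It is 67% only when *K* = 0. If *K* = 6*d*, it is 4*d*/12*d* = 33%.
- If the intervention saves *s* per month, the full figure is *K* − 6*s* and the summed figure *K* − 2*s*. With *K* = 4*s* these are −2*s* and +2*s*, so the sign changes.

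The values of *K* relative to *d* or *s* are assumptions; the article gives no costs.

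**3. If a scaling rule is used.** Assume, for one arm, £200 in month 1 and £100 in month 6 (assumed values).

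- Summed: 200 + 100 = £300
- Month-6 rate carried back: 200 + 5 × 100 = £700
- Linear between months 1 and 6: 200 + (180 + 160 + 140 + 120) + 100 = £900
- Month-1 rate carried forward: 5 × 200 + 100 = £1,100

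The three scaling rules alone range from £700 to £1,100 on identical data.

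**4. Units.** For items m and n the wording of the question and the label of the answer space disagree, each carrying the other's unit. The day-case definition rules out *nights* for item m. Every hospital row has a unit, so a simple column shift in the extracted text does not explain it. As an illustration, a 10-night stay entered as one *time* and costed per night would count at one tenth.

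**The case against.** The strongest reply is that the article does not say how one-month reports become a 6-month cost. It refers to cost profiles, regression-based mean differences and sensitivity analyses, and a scaling rule is the kind of detail left to a health economics plan that is not shown. QALYs, too, span six months only by interpolation between two measurements. A short recall on a piloted form is a defensible trade-off against poorer memory over five months. The unit labels may be a typesetting slip in the article.

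Much of this stands. A reader might infer that the incremental cost is wrong by construction, that the ICER is understated by 67%, or that the threshold comparison is invalid. The documents do not support that: nowhere is it stated that the two months are added, and delivery cost is outside the recall window. Nor do they show that the exchanged labels were on the form participants completed.

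What does not stand is that a later plan could close the gap. The recall window is a data-collection choice. The planned multiple imputation deals with answers that are missing, not with months nobody was asked about. A scaling rule would supply an assumption for those months, not data.

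**Conclusion.** The point holds in a limited form. On the printed text, healthcare use is observed for 2 of the 6 post-randomization months, against a 6-month horizon and QALYs integrated over the whole of it. The one-third weight on healthcare cost differences applies only if the reports are summed and the monthly difference is constant. The effect on the ICER depends on delivery cost and on a rule for months 2 to 5 that the article does not state. Under any rule, two-thirds of the healthcare cost period is assumed.

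The conclusion rests on Table 3 being the form used at all three visits and on there being no records-based source for follow-up service use; none is named. The unit mismatch is certain in the article and unconfirmed in the field. Cost-effectiveness is a stated secondary objective; the abstinence outcome is unaffected.

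**What to change.** **Forms still to be collected at 6 months.** Ask about the period since the 1-month questionnaire, at least for the hospital items, and record which recall version each participant received. The cost is less accurate recall and a mixture of windows within one outcome. Recruitment was planned to end with 2024, so few or no forms may remain and the analysis change may be the only one available.

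**Data collected with the one-month window.** Pre-specify before analysis that:

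- the two observed months are not summed as the 6-month cost;
- the base case is an interpolated (area-under-the-curve) healthcare cost between months 1 and 6, with delivery cost added from trial records;
- sensitivity analyses vary months 2 to 5, for example by carrying the month-1 rate forward and the month-6 rate back;
- the report states that months 2 to 5 were not observed.

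This needs analysis wording only. Interpolation is itself an assumption and is weakest for rare, expensive events such as admissions.

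**Items m and n.** Compare the article with the fielded form. Day cases should be answered in times and inpatient stays in nights. If only the article is wrong, correct the table. If the exchanged labels were fielded, correct the form and query non-zero entries on both items.

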### Usual care and relevant contextual factors

Details and characteristics of the ‘usual care’ provided to the control group at each site will be collected at the end of the trial for assessment in the analysis. We will also document relevant contextual factors through the day‐to‐day and monthly scheduled communication between sites and the trial management and coordination team.

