Electronic cigarettes (e‐cigarettes), which provide nicotine without many of the harmful substances found in tobacco smoke, are increasingly recognized as a valuable tool for smoking cessation for people with mental illness [8]. In England, there has been an increase in their use as a smoking cessation tool [9, 10], with nicotine‐containing e‐cigarettes being included as a treatment component in national guidelines on the treatment of tobacco dependence [11]. In the general population, accumulating evidence indicates that nicotine e‐cigarettes are more effective than nicotine replacement therapy (NRT) in aiding smoking cessation [12, 13, 14]. Additionally, research conducted in Italy [15, 16], the USA [17], Australia [18] and the UK [19] suggests that e‐cigarettes can be effective for smoking cessation and reduction among adults with mental illness who smoke. While cessation remains the ideal outcome, smoking reduction also highlights the potential to reduce morbidity and mortality associated with smoking, as even partial reductions in cigarette consumption can yield health benefits [20]. Importantly, these studies did not find any evidence that e‐cigarettes adversely affect mental health, further emphasising their potential as a safe smoking cessation aid for individuals with mental illness. In fact, the uptake of e‐cigarettes appears particularly high among people with mental illness, who have been shown to be more likely to have tried and to currently use e‐cigarettes than the general population [21]. Several factors may contribute to this. First, e‐cigarettes are relatively inexpensive compared with both cigarettes and other cessation treatments [22]. Second, they offer a straightforward stand‐alone treatment that is easy to use. Third, unlike most NRTs, e‐cigarettes mimic the sensory experience of smoking and allow users to control their nicotine intake, which may appeal to people who are more dependent upon smoking and have previously struggled to quit [23]. As such, e‐cigarettes could be an important aid in efforts to address tobacco‐related health inequalities in this population, which has been identified as a health priority in England [24, 25]. As service models to improve the provision of tobacco dependence treatment are being rolled out across the country [25], it is important to advance the evidence base on the role that e‐cigarettes can play in these efforts.

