### Treatment groups

#### Control

Participants in the control group will receive usual care related to smoking cessation in accordance with UK National Institute for Health and Care Excellence (NICE) guidelines. Usual care, which is free to access in the UK, varies between trusts and GP practices but is guided by NICE guideline NG209 [11]. At a minimum, it should include evidence‐based and very brief advice to stop smoking, which consists of the three As (Ask and record smoking status; Advice on the best way of quitting; and Act on patient response to build confidence) [29, 30], and a referral to in‐house or external specialist stop‐smoking services. Participants, regardless of their motivation to stop smoking, will be encouraged to consider quitting and to set a target quit date within a week of randomization. Those who do not wish to set a target quit date will be encouraged to reduce their cigarette consumption.

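### Usual care can include service-supplied e-cigarettes, but the service use questionnaire has no item that counts them, so they drop out of the incremental cost

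*Protocol article*

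**What the plan says.** Five places in the protocol article bear on this.

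- **Introduction.** Nicotine e-cigarettes are described as "being included as a treatment component in national guidelines on the treatment of tobacco dependence", citing reference 11.
- **Treatment groups, Control.** Usual care "varies between trusts and GP practices but is guided by NICE guideline NG209", again reference 11, and should at least include very brief advice and referral to stop-smoking services. The Intervention section gives the kit in addition to this same care.
- **Economic evaluation.** Everyone has access to usual care, and "the use of currently available smoking cessation aids will be collected using a service use questionnaire" at baseline, 1 month and 6 months.
- **Health economics, Table 3.** The questionnaire is printed item by item, a to p. It asks about the past month and about services not provided by the trial. It names NRT, bupropion and varenicline prescriptions. Item j then asks "How many prescription items have you received other than NRT, Zyban or Champix". No item mentions e-cigarettes.
- **Usual care and relevant contextual factors.** Information on the care "provided to the control group at each site will be collected at the end of the trial for assessment in the analysis". The next sentence, beginning "We will also document relevant contextual factors through the", refers to day-to-day and monthly communication with sites.

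**The concern.** The economic evaluation says that a particular instrument captures the cessation aids in use, and the instrument as printed omits one that usual care may supply. This is not a detail left to a longer document, because the article gives both the statement and the questionnaire, and they do not match. Under the NHS and personal social services perspective, an e-cigarette paid for by a service is a cost. If it has no recorded quantity, it enters the analysis as nothing.

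The site-level description of usual care could show where such supply happens, but it is gathered once, at the end, and names only the control group. The Introduction says that new service models for tobacco dependence treatment are being rolled out, so usual care may change during the trial. One closing description may not fit what earlier participants received.

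**Working it through.** **Can usual care contain e-cigarettes?** The Introduction and the Control section both rest on reference 11. The first says it includes nicotine e-cigarettes; the second says it guides usual care, with variation between sites. No section excludes them from usual care. The exclusion criteria remove only people who already use them at least weekly. So supply by a service is possible in either arm. How often it happens is not stated.

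**Where would a service-supplied e-cigarette be recorded?**

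| Item | What it captures | Service-supplied e-cigarette |
|---|---|---|
| Table 3, a–f | Contacts with staff, services and helpline | The contact, not the product |
| Table 3, g–i | NRT, bupropion, varenicline prescriptions | Not captured |
| Table 3, j | Other prescription items | Only if prescribed, and then not identifiable |
| Table 1, e-cigarette use at 1 and 6 months | Use | Not who supplied or paid, as described |
| Secondary outcomes, device question | Study device or not | A non-study device may be bought privately or supplied by a service |

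Footnote a to Table 3 counts a device as a prescription item, so item j could include a prescribed e-cigarette, but without a label that would let a unit cost be attached.

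**Effect on incremental cost.** The plan gives no figure to reproduce. Let s_C and s_I be the mean number of service-supplied kits per control and per intervention participant that go unrecorded, and C the unit cost to the NHS.

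True incremental cost = recorded incremental cost + (s_I − s_C) × C

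Error (recorded − true) = (s_C − s_I) × C

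Neither s_C, s_I nor C is in the documents. The values below are assumptions that show the range and the sign.

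| s_C | s_I | Error in incremental cost |
|---|---|---|
| 0.2 | 0 | (0.2 − 0)C = 0.2C, overstated |
| 0.2 | 0.1 | (0.2 − 0.1)C = 0.1C, overstated |
| 0.2 | 0.2 | 0 |
| 0.1 | 0.2 | (0.1 − 0.2)C = −0.1C, understated |

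For a positive QALY difference ΔQ, the ICER shifts by the same error divided by ΔQ.

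**The case against.** Much of what surrounds usual care is measured. Participants report cessation sessions, staff contacts for smoking and the named medicines at baseline, 1 month and 6 months, with no restriction by arm. Contextual factors are documented throughout the trial. Only the site-level summary waits until the end, and since the Intervention section refers back to the same usual care, a site's description may in practice serve both arms. The e-cigarette questions are not reproduced, so they might ask about source. If control participants receive more kits, the omission makes the intervention look dearer, which is conservative. All of this stands. It limits the point to one missing quantity and to the timing and scope of one record. It does not supply the quantity, because the Economic evaluation section names the service use questionnaire as the source.

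A reader might infer more: that the trial cannot tell a weak intervention from an active control, or that it loses power. The documents do not support this. The objective is to compare offering the kit with usual care as it is given, and that randomised contrast is valid whatever usual care contains. E-cigarette use is scheduled at both follow-ups, and an as-treated analysis is planned for use by controls.

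On power, the stated figure reproduces. With 308 per group and 5% against 13.1%, the pooled-variance normal approximation gives 94.1% (92.2% with continuity correction), so above 90% as claimed. If 10%, 20% or 30% of controls were supplied and gained the full effect, the control rate would be 5% + share × 8.1 points, that is 5.8%, 6.6% or 7.4%, and power 87.3%, 77.1% or 64.1%. But these shares are invented. The feasibility study reported limited contamination, and the 5% control rate was set in the light of that study's controls, so adding contamination may count it twice. Better recording would not restore power either.

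Nor does the text say that usual care will be recalled from memory, or that sites will have seen results by arm when they describe it.

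**Conclusion.** The point holds as a gap in costing and in the record of usual care. Followed as written, e-cigarettes supplied by a service without a prescription have no quantity in the economic evaluation, and prescribed ones cannot be identified. The error in incremental cost is the between-arm difference in that supply times its unit cost. Its sign depends on which arm receives more, and its size cannot be set from the documents. A figure such as 0.2C is a net error only if intervention participants receive no service kits. The conclusion assumes that e-cigarette supply and its payer are not recorded by questions that the article does not print.

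The end-of-trial, control-only description of usual care is a lesser weakness of the same kind. The primary analysis is not called into question. The change is worth making because it is cheap and because the article's statement about its own instrument is otherwise not met.

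**What to change.** 1. Add a row to Table 3 for e-cigarettes or kits supplied by an NHS or stop-smoking service outside the trial, ask it in both arms, and apply a unit cost. Where follow-up is already complete, state the limitation and vary the assumed supply by arm in a sensitivity analysis.
2. Record each site's usual care for both arms, including whether the site or its stop-smoking service supplies e-cigarettes. Do this at site opening or, for sites already open, now and before outcome data are analysed. Update it at the monthly contacts already planned.

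The cost is one questionnaire row, one short site form and slight extra burden. Participants followed up before the change will lack the new item, and the row inherits the questionnaire's one-month recall, so supply between the two follow-up windows is still not observed directly. An analysis of the treatment effect by whether a site supplies e-cigarettes could be added as exploratory, but with a minimum of 11 sites it would have low power and is not needed to close this gap.
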